| **Study category and Rationale** | Category C: Study involving radiopharmaceuticals without approval in Switzerland |
| **Clinical Phase:** | Phase I/II study |
| **Background and Rationale:** | The aim of this study is to provide robust data on the head-to-head comparison of the two ligands of PSMA available in Switzerland for PET-imaging, i.e. ^68^Ga-PSMA-11 und ^18^F-PSMA-1007. |
| **Objective(s):** | The overall objective is to compare the performance of the new radiotracer for the investigation of prostate cancer (^18^F-PSMA-1007) in a head-to-head comparison with the existing standard-of-care (^68^Ga-PSMA-11).  The primary objective is to assess non-inferiority of the new tracer with respect to the proportion of patients with pathological PSMA-positive findings.  Secondary objectives are   - to provide a head-to-head comparison of tracer kinetics - to compare the number of pathological, benign and uncertain lesions found with the two tracers - to determine the intra-reader agreement for the two tracers - to compare the proportion of pathological lesions confirmed in a follow-up between the two tracers - to compare tumour visibility between the two tracers   to evaluate safety and tolerability for the two tracers |
| **Outcome(s):** | PRIMARY ENDPOINT  The primary endpoint is the proportion of patients with a pathological PSMA-positive finding (= positivity rate) at one time-point (2h) with the existing standard-of-care (^68^Ga-PSMA-11) compared to the new tracer (^18^F-PSMA-1007).  SECONDARY ENDPOINTS   - Intra-individual comparison of the parametric imaging parameter K*_D_* (measure of tracer affinity) for the two radiotracers. - The number of pathological, benign and uncertain lesions for each tracer in five regions (prostate bed, pelvic lymph nodes, extra-pelvic lymph nodes, bone, or other organs) classified by six blinded readers (three for each tracer) using previously published interpretation guidelines (PSMA-Rads 1.0) - Inter-reader reliability between the three readers for each tracer on the level of the region with respect to three categories (pathological, benign, uncertain). - The region-based positive predictive value (PPV), i.e. the percentage of pathological lesions that are confirmed pathological at the twelve months follow-up (based on the subset of patients and lesions with follow-up data at twelve months). - Tumour visibility will be compared by means of uptake values (SUV) as well as tumour to background contrast in a lesion based analysis. The tumour to background ratio (TBR) is defined as lesion SUV ÷ SUV of reference background region, where the background uptake is defined by convention as the left gluteal musculature. - Number and severity of adverse events per tracer (up to 48h follow up).   OTHER ENDPOINTS OF INTEREST  In a second round of tumour classification, two readers (in consensus) will classify each lesion as pathological, benign or uncertain in a lesion-specific approach and perform a lesion based follow-up to assess PPV on the lesion level. |
| **Study Design** | *A prospective, single centre, open label, dual arm randomised cross-over, non-inferiority trial comparing the new tracer (^18^F-PSMA-1007) with the standard tracer (^68^Ga-PSMA-11) in biochemically recurrent prostate cancer.*  *The study is designed using the Standards of Diagnostic Accuracy (STARD) checklist. The study is initiated, planned and will be conducted and analysed by the investigators. Financial support is provided the Werner und Hedy Berger-Janser Foundation, the Bernese Cancer league and the Direktion Lehre und Forschung, Inselspital Bern. The second tracer for the second PET is provided by either SWAN Isotopen AG or Unilabor Bern. All data will be collected in a central trial database.* |
| **Inclusion / Exclusion criteria:** | *Inclusion Criteria*   - Patients with known biochemical recurrence of a histologically confirmed prostate cancer post radical prostatectomy, defined as two consecutive PSA values > 0.2 ng/ml: - Post prostatectomy: Patients > 18 y/o - PSA measured within ± 4 weeks of the first PSMA-PET/CT - Patients providing written informed consent - No change in PC treatment in the period between the first and second scans   *Exclusion Criteria*   - Patients receiving ADT within 6 months prior to the PSMA-PET/CT - Patients with contraindication to diuresis with 20mg Furosemide - Patients with renal dialysis or relevant renal impairment (eGFR < 35 ml/min) - Inability to provide written informed consent - Inability to schedule and attend two consecutive PET examinations - Patients undergoing active treatment for a second non-prostatic malignancy at the time of the first scan. - Known sensitivity or allergy to PSMA-ligands or one of the components of the radiotracer solutions used. |
| **Measurements and procedures:** | All patients will undergo scanning with both radiotracers, affording an intra-patient comparison of both tracer types. The PET scans will be analysed with respect to number of lesions detected and tracer uptake (SUV) for pathological lesions. |
| **Study Product / Intervention:** | In this cross-over trial, patients will be randomised to one of two tracer sequences, ^68^Ga-PSMA-11 first or ^18^F-PSMA-1007 first. Patients will undergo a scan with the first radiopharmaceutical, and a second scan at earliest after a period of 2 days and at latest 2 weeks. |
| **Control Intervention (if applicable):** | Intra-patient comparison with both radiotracers. |
| **Number of Participants with Rationale:** | Recruitment will be open until 100 patients have been recruited.  Assuming that 80% of the patients are positive for each one of the tracers and that 75% of the patients will be positive for both tracers, recruitment of 100 patients will give a power of 85% to detect non-inferiority with a non-inferiority margin of -10% and a one-sided alpha of 2.5% using the Wald confidence interval for paired proportions with the Wald Bonett-Price Laplace adjustment. |
| **Study Duration:** | 2 years |
| **Study Schedule:** | First patient examination: June (planned) 2022*  Last patient examination: June 2023*  Follow-up of 6 months (until end of Dec 23)*  Data analysis and publication within 6 months (until June 2024)*  * See additional text in Section “Study Schedule” |
| **Investigator(s):** | Sponsor: [name]. med. [name]  Principal Investigator: [name]. med. [name]  Klinik für Nuklearmedizin, Inselspital Bern  [name]  [name]  [contact]  [contact] |
| **Study Centre(s):** | Single-centre (University Clinic for Nuclear Medicine, Inselspital Bern) |
| **Statistical Considerations:** | **Primary Endpoint:**  The primary outcome (proportion of patients with PSMA-positive pathological lesions = patient based sensitivity) will be compared between tracers using an absolute risk difference (new tracer minus old tracer) with a one-sided lower 95% confidence interval for paired proportions (Wald with Bonett–Price Laplace adjustment). If the lower limit lies above -10%, we will claim non-inferiority. Detection rates per patient will be based on majority consensus reads.  **Secondary Endpoints:**   - Parametric imaging will be performed for the two radiotracers in a subset of patients (n=10*), allowing comparison of the tracers’ dosimetric and kinetic parameters, with affinity for the PSMA radioligand by calculation of the parametric equilibrium constant *K*_D,_ which will be compared between the two tracers with descriptive statistics. - The number of PSMA-positive lesions defined as pathological, benign and uncertain per region will be compared using mixed-effects Poisson regression. Patient-level data will also be analysed using the Wilcoxon signed-rank test.. - Inter-reader reliability will be compared on the region level using Krippendorff’s alpha for benign, pathological and uncertain lesions, separately for the two tracers. - Region based PPV will be calculated for each tracer separately with 95% Wilson score confidence intervals. The two tracers will be compared using McNemar’s test and an absolute risk difference with 95% confidence interval. - Semi-quantitative tumour to background ratio (defined as lesion SUV ÷ SUV of reference background region, where the background uptake is defined by convention as the left gluteal musculature) will be summarised on a region-level (i.e. using the mean over all positive lesions per region). Summarised data will be analysed using linear mixed-effects regression models. - The number and severity of adverse event will be analysed using descriptive statistics. All serious adverse events will be listed.   *The requirement for N=10 patients is justified on the previous dosimetry paper for the established PET radiotracer ^68^Ga-PSMA-11 which was adequately powered to demonstrate a mean-effective dose of 0.023 ± 0.004 mSv/MBq, i.e. with a precision in the µSv range [1]. |
| **GCP Statement:** | This study will be conducted in compliance with the protocol, the current version of the Declaration of Helsinki, the ICH-GCP as well as all national legal and regulatory requirements. |

Abbreviations

| ADT | Androgen deprivation therapy |
| --- | --- |
| AE | Adverse Event |
| BASEC | Business Administration System for Ethical Committees, (https://submissions.swissethics.ch/en/) |
| CA | Competent Authority (e.g. Swissmedic) |
| CEC | Competent Ethics Committee |
| CRF | Case Report Form |
| ClinO | Ordinance on Clinical Trials in Human Research *(in German: KlinV, in French: OClin, in Italian: OSRUm)* |
| eCRF | Electronic Case Report Form |
| CTCAE | Common terminology criteria for adverse events |
| DSUR | Development safety update report |
| GCP | Good Clinical Practice |
| IB | Investigator’s Brochure |
| ICH | International conference on harmonisation of technical requirements for registration of pharmaceuticals for human use |
| Ho | Null hypothesis |
| H1 | Alternative hypothesis |
| HRA | Federal Act on Research involving Human Beings *(in German: HFG, in French: LRH, in Italian: LRUm)* |
| IMP | Investigational Medicinal Product |
| IIT | Investigator-initiated Trial |
| ISO | International Organisation for Standardisation |
| ITT | Intention to treat |
| MD | Medical Device |
| MedDO | Medical Device Ordinance *(in German: MepV, in French: ODim)* |
| PI | Principal Investigator |
| SDV | Source Data Verification |
| SOP | Standard Operating Procedure |
| SPC | Summary of product characteristics |
| SUSAR | Suspected Unexpected Serious Adverse Reaction |
| TMF | Trial Master File |

PC Prostate-Cancer

PET/CT Positron emission tomography/computed tomography

p.i. post injection of radiotracer

PPV Positive Predictive Value

PSMA Prostate specific membrane antigen

SUV standard uptake value

*SUVmax* = maximum SUV measured within a lesion

*SUVpeak =* defined as the average of a small, fixed region of the ROI (typically defined at 40% of the maximum) and is less vulnerable to image noise than SUVmax.

*SUVmean* = mean SUV measured within a volume of interest

StSV Strahlenschutzverordnung (814.501)

TBR tumour to background ratio

TNM International union against cancer classification of tumours (8^th^ Ed.)

ROI region of interest

VOI volume of interest

Study schedule

[figure not shown]

[figure not shown]

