## Clinical Evidence to Date

This investigation for these two radiopharmaceuticals will be the first such head-to-head comparison for this patient group. By definition, no systematic reviews are available. We are aware of no evidence of any reports of adverse safety profile, history of modification or recall of either of the substances.

We note one pilot study comparing these two radiotracers by Kuten et al., albeit in in a small cohort of primary prostate cancer patients and not in recurrent prostate cancer and in a study which did not conform to standard trial methodology [17]. Likewise, a retrospective comparison by Rauscher et al [13] exists, showing no inferiority between ^68^Ga-PSMA-11 PET and ^18^F-PSMA-1007 PET, although no sample size or power estimate was included. Both studies used a two point scale (binary positive/negative) and did not consider the possibility of diagnostic uncertainty, which is an under-investigated phenomenon and which this study seeks to address. A small case series reported increased diagnostic certainty for lesions in close proximity to the bladder with additional ^18^F-PSMA-1007, although we note the lack of diuretics for ^68^Ga-PSMA-11 as major weakness of this study [15]. This will be the first clinical study of prospective, randomised design conforming to standards for evidence-based medicine. The study design incorporates reduction of bladder activity through diuretic use, in-keeping with clinical evidence and guidelines. Diagnostic certainty in these tracers has hitherto been inadequately studied.

We note that PSMA radioligand uptake can be non-specific [16], and that non-prostatic tracer uptake is reported as increased in ^18^F-PSMA-1007 compared to ^68^Ga-PSMA-11 [13]. We consider this latter point to be of high clinical relevance: unnecessary additional diagnostic testing or treatment can result from diagnostically uncertain lesions.

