# STUDY OUTCOMES

## Primary Outcome

The primary endpoint is the proportion of patients with a pathological PSMA-positive finding (= detection rate) at one time-point (2h) with the existing standard-of-care (68Ga-PSMA-11) compared to the new tracer (^18^F-PSMA-1007).

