### Response Criteria

Response to targeted treatment (surgery, radiotherapy) will be considered as confirmatory in the case of a fall in PSA, using previously published response criteria [22]. Where PET scan findings are recorded as positive, but the follow up refutes this, the scan will be recorded as false positive. Established RECIST (Vers 1.1) criteria will be used to interpret correlative imaging [23]. The details are as follows:

Follow up of clinical notes to 6 months will be performed for histopathological data, additional conventional imaging (CT, MRI and or bone scintigraphy), PSA change following focal salvage therapy (where no systemic therapy has been applied. Follow-up imaging will be performed by local read.

1. **Follow up histology**

Positive biopsy or histology will be taken to be confirmatory.

For negative biopsies: to rule out false negative imaging for image-guided biopsy will be reviewed. For lymph node biopsies, comparison of the PET/CT and follow-up (post intervention) imaging will be made to confirm that biopsy of the correct node occurred.

1. **Follow up imaging**

No established imaging criteria are available for a number of imaging modalities in recurrent prostate cancer. To enable comparison of these data with previous imaging trials, the imaging criteria as previously published by Fendler et al. will be used (§2.1.5.3 of Supplementary Materials 2: Trial Protocol [24])

1. **Follow up following local treatment**:

PSA change following radiation therapy will be according to previously published criteria, with a PSA response of > 50% taken to be confirmatory [25] (see figure 4).

[figure not shown]

**Fig.4.** Example interpretation criteria for patients undergoing biopsy or radiotherapy (with and without systemic hormone deprivation therapy) image from Emmett et al. [25]

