## Determination of Sample Size

Power was determined using Monte Carlo simulations with 1000 repetitions and the following assumptions:

- Marginal probabilities: 80% of the patients are positive for tracer A and 80% are positive for tracer B
- Both tracers are applied to each patient
- Non-inferiority design with a one-sided alpha of 2.5%
- Non-inferiority margin of -10% (clinically acceptable margin in detection rate, balanced against the requirements for clinically realistic number of patients). We justify this margin as being less than 50% of the margin reported for superiority (22%) in a prospective trial published for ^68^Ga-PSMA-11 versus the first-generation tracer ^18^F-Choline [22].
- Non-inferiority is concluded if the lower limit of a 95% confidence interval (Wald with Bonett–Price Laplace adjustment) for the difference in the proportion of tracer-positive patients (new tracer – old tracer) is larger than the non-inferiority margin
- A pragmatic assumption is made regarding the correlation of the paired measurements. Limited data are available for this, given the dearth of comparative studies. Neither retrospective analyses [28] nor limited pilot studies [17, 27] have demonstrated any difference in detection rate. We take a worst-case scenario, and assume that both tracers are positive for 75% of the patients.

Data was simulated using function rmvbin from R package bindata [29]. With 100 patients we will have a power of 85% to detect non-inferiority.

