### Primary Analysis

The primary outcome (proportion of patients with PSMA-positive pathological lesions) will be compared between tracers using an absolute risk difference (new tracer minus old tracer) with a one-sided lower 95% confidence interval (CI) for paired proportions (Wald with Bonett–Price Laplace adjustment). If the lower limit lies above -10%, we will claim non-inferiority. Proportion of pathologic scans will be based on majority consensus reads.

The number of PSMA-positive lesions defined as pathological, benign and uncertain in each region will be analysed using separate mixed-effects Poisson regression models with tracer as fixed covariate and nested random effects for patient and region. We will report incidence rate ratios with 95% CI and p-values. As a sensitivity analysis we will compare the number over all regions using the Wilcoxon signed-rank tests and the Mann-Whitney statistic with 95% CI.

Inter-reader reliability will be analysed on the region-level based on the number of benign, pathological and uncertain lesions determined by each reader. We will calculate Krippendorff’s alpha with a ratio difference function and bootstrap 95% CI separately for each tracer.

Lesion-based PPV will be calculated for each tracer as the proportion of pathological lesions confirmed pathological during follow-up among all lesions with a known state and will be presented with 95% Wilson score CI. Using all lesions with a confirmed status during follow-up, the two tracers will be compared using McNemar’s test and an absolute risk difference with 95% confidence interval.

The semi-quantitative tumour to background ratio will be summarized on a region-level (i.e. using the mean over all positive lesions per region) and analysed using a linear mixed-effects regression model with tracer as fixed covariate and patient and region as nested random effects. The mean difference with 95% CI will be reported.

For the subset of patients with additional parametric imaging data (N=10) the planned analysis of parametric imaging parameters (see first secondary endpoint) is planned prior to completion of the study. This exploratory analysis of this secondary endpoint will not assess the primary endpoint and will not influence further trial conduct or further trial process.

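### The synopsis equates the primary outcome with sensitivity, but it is a positivity rate with no reference standard, so false positives on the new tracer could mask a loss of detection

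*Protocol*

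**What the plan says.** One quantity carries three names.

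- Study synopsis, Statistical Considerations: "The primary outcome (proportion of patients with PSMA-positive pathological lesions = patient based sensitivity".
- Study synopsis, Outcome(s): "proportion of patients with a pathological PSMA-positive finding (= positivity rate) at one time-point (2h".
- Section 5.1, Primary Outcome: "The primary endpoint is the proportion of patients with a pathological PSMA-positive finding (= detection rate) at one time-point (2h".

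Section 11.4.2 fixes how a patient becomes positive, "Proportion of pathologic scans will be based on majority consensus reads", and how the result is judged, "If the lower limit lies above -10%, we will claim non-inferiority". Neither statement refers to histology, follow-up imaging or PSA response, and neither do the hypotheses in section 11.1.

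Truth enters elsewhere. Section 6.1.4 states: "Where PET scan findings are recorded as positive, but the follow up refutes this, the scan will be recorded as false positive". The positive predictive value (PPV) is a secondary endpoint, by region in the synopsis and section 5.2 and by lesion in section 11.4.2. Section 9.2.2 calls the follow-up of pathological lesions explorative and says that confirmation exists only where clinical care leads to it. On the new tracer, section 3.4 notes that "non-prostatic tracer uptake is reported as increased in ^18^F-PSMA-1007 compared to ^68^Ga-PSMA-11" and regards this as clinically important.

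**The concern.** Sensitivity counts correct positive calls among diseased patients. The positivity rate counts all positive calls. The two coincide here only if every patient called pathological has at least one truly malignant focus behind the call. The protocol does not assume this, since section 6.1.4 provides for scans to be labelled false positive. That label is not carried into the primary count, and no patient-level analysis described in the protocol uses it.

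The direction matters in a non-inferiority trial. The tracer with more non-specific uptake gains positivity from any of it that readers call pathological. If the result were then reported as sensitivity, readers could take it to mean that the new tracer misses little disease, which the primary comparison does not show. PPV does not close the gap: it describes the positive calls that were followed up and says nothing about disease that was missed.

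**Working it through.** **Inputs from the protocol.** N = 100; margin −10%; "Non-inferiority design with a one-sided alpha of 2.5" per cent; Wald interval with Bonett–Price Laplace adjustment; 80% positive on each tracer and 75% on both; stated power 85% (section 11.2).

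**Inputs that are assumptions.** All true-loss and false-positive rates below. The documents give none.

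**Step 1: decision rule.** Let b be the number of patients positive on the new tracer only and c the number positive on the old tracer only. With p₁ = (b+1)/(n+2) and p₂ = (c+1)/(n+2),

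lower limit = p₁ − p₂ − z·√{[p₁ + p₂ − (p₁ − p₂)²]/(n+2)}, with z = 1.96.

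Non-inferiority is claimed if this exceeds −0.10. Probabilities come from exact enumeration of (b, c) under the trinomial distribution.

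**Step 2: the plan's own figure.** 80% − 75% = 5% discordant in each direction. Exact power is 0.865. The plan states 85% from 1000 simulations, whose standard error is √(0.85 × 0.15/1000) = 0.011. The figure reproduces.

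**Step 3: why positivity can hide a loss.** For each tracer let T be the share of patients with at least one truly malignant focus called pathological, and F the share called positive only on non-malignant foci. Positivity = T + F, so

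difference tested = (T_new − T_old) + (F_new − F_old).

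A positive second term offsets a negative first term one for one.

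**Step 4: illustration.** Take 10% of patients as truly positive on the old tracer only, no true new-only detections, and no false-positive-only patients on the old tracer. The true loss is then 10 points, equal to the margin. Let a share f of all patients be falsely positive on the new tracer only. With 80% positive on the old tracer, the old-negative group is 20%, so f is f/0.20 of that group.

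| f | Share of old-negative patients | Observed difference | Chance of claiming non-inferiority |
|---|---|---|---|
| 0% | 0% | −10 points | 0.058 |
| 2% | 10% | −8 points | 0.110 |
| 5% | 25% | −5 points | 0.257 |
| 8% | 40% | −2 points | 0.458 |
| 10% | 50% | 0 points | 0.595 |

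Hand check at the expected counts. For b = 10, c = 10: p₁ = p₂ = 11/102 = 0.1078, and the limit is −1.96 × √(0.2157/102) = −0.090, so non-inferiority is claimed. For b = 0, c = 10: p₁ − p₂ = −10/102 = −0.0980, and the limit is −0.0980 − 1.96 × √(0.1080/102) = −0.162, so it is not.

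The first row exceeds 0.025 because with b = 0 the claim is made whenever c ≤ 5, which has probability 0.058 at a 10% rate.

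**Step 5: a second structure.** Suppose instead that 5% are truly positive on the new tracer only and 15% on the old only (again a 10-point loss), and that false-positive-only calls are spread proportionally over all patients without a true-positive new scan. The chances are 0.027, 0.20, 0.60 and 0.92 with 0%, 5%, 10% and 15% of patients falsely positive. The pattern does not depend on one particular set-up.

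**The case against.** The other side has several good points.

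- **The label is local.** Sensitivity appears only in one parenthesis of the synopsis. The primary objective, the hypotheses and section 11.4.2 speak of the proportion with pathological positive findings.
- **The endpoint is an open choice.** Confirmation depends on clinical care, so a reference standard was not available for everyone. All patients have biochemical recurrence (section 7.1), which brings positivity close to sensitivity at patient level. It does not make them equal, because a patient with recurrence can be called positive on a benign focus while the true site is missed.
- **A positive call must pass filters.** Section 6.1.2 requires PSMA-RADS-type criteria, a separate uncertain category, readers with at least 100 scans on their tracer, training on pitfalls, and a majority of three. These should reduce false positives, but none removes a refuted one from the primary count.
- **False positives are studied.** PPV and the counts of benign and uncertain lesions are compared between tracers. Neither enters the non-inferiority decision.
- **The largest illustrated figure is near a worst case.** At f = 10%, half of all old-negative patients would have to be falsely called pathological by a reader majority.

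A reader might infer that the non-inferiority test is invalid, or that the new tracer is expected to gain a false advantage of known size. The documents support neither. The test is sound for positivity as defined. Section 3.4 reports more non-prostatic uptake, not more majority pathological calls, and links its concern to uncertain lesions.

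**Conclusion.** The point holds as a mislabelled primary outcome with a real consequence for interpretation. The synopsis states an equivalence that is wrong, and the three names should be one. Within the stated rules, a scan the protocol itself would record as false positive counts as a success, so a non-inferior positivity rate does not establish non-inferior sensitivity.

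The size is unknown. Under the assumptions of step 4, a true loss equal to the margin would be declared non-inferior with probability 0.11 to 0.60 as new-only false positives run from 2% to 10% of patients, against 0.06 with none. These figures assume no false-positive-only patients on the old tracer; only the excess on the new tracer matters. They use the one-sided 2.5% level of section 11.2. Section 11.4.2 instead describes a one-sided 95% limit, which is a separate inconsistency; at that level the 0.60 becomes 0.72.

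**What to change.** 1. In the synopsis statistics row, delete the equation with patient-based sensitivity. Use *positivity rate* throughout, including section 5.1, and state that the non-inferiority conclusion concerns positivity.
2. Add one prespecified supportive analysis at patient level: the same paired difference, new minus old, with a 95% confidence interval, on follow-up data already being collected. Give two versions. (a) A patient is positive on a tracer only if at least one pathological region on it is confirmed, so refuted and unverified positives do not count. (b) Only refuted positives are removed, and unverified ones stay.
3. Report both versions beside the primary result, without a pass/fail gate. A rule that the supportive estimate must not favour the old tracer might look attractive, but two equal tracers with 5% discordance in each direction would give an estimate of at least zero only about 56% of the time, against 86.5% for the primary test.

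The cost is a wording change and one extra paired analysis. The headline claim becomes narrower. The supportive analysis will be less precise and will depend on which patients are worked up clinically (section 9.2.2), with record review unmasked (section 6.1.2); showing both versions makes that dependence visible.
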